#### Secondary outcome measures

Psychophysiological parameter: A heart rate wrist band will be used to record the real time response to VRET at T1 during VRET session. The device will be integrated with the VR software and the output will be recorded during therapy.Subjective Units of Distress (SUD) scale: The SUD scale is an eleven-point scale [39] to measure the intensity of subjective distress currently experienced by an individual. It is used by the therapist in desensitization based therapies as a standard to evaluate the progress of the therapy. Typically the patient is asked by the therapist “On a scale of 0-10 where, 0 is no discomfort and 10 is the worst, how do you feel right now”. The researcher will record the SUDS scores during each VR scenario exposure of the VRET session. During the VRET session each VR exposure is repeated, until there is habituation demonstrated by a relatively low SUD score (≤2), and the next scenario is introduced. The total number of VR exposures with each VR scenario that was required to achieve SUDS score of ≤2 will be summed up and recorded by the researcher post-therapy.VR experience: will be evaluated at T1.Time perception is determined by asking the participants to calculate approximately the duration of VR immersion with therapy [40] and the ratio of subjective and objective duration will be evaluated.Presence will be measured using an 11-point verbal rating scale (VRS) [41].Realism will be indexed with an 11-point (VRS) [41].Severity of nausea (‘cybersickness’) will be measured using an 11-point VRS [41].Intention to use VR goggles again will be indexed with a yes/no response.Intention to revisit the dental surgery will be measured with a yes/no response.

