##### Experimental phase

In this phase, participants are exposed to five different VR scenarios (Idle, Mirror, Syringe, Drill with no sound, Drill with sound). The duration of each exposure will be 35 seconds. The interactive part of the simulated dental environment will be controlled by the researcher using the tool selection option on the UI window of the computer. The researcher will be able to control the playback of the VR scenarios.

VRET is conducted using a pre-determined hierarchy as follows:Scenario #1 (Idle). This shows a dental operatory with various instruments surrounding the patient’s chair and a virtual dentist sitting next to the patient’s right hand inside the 3D scene.Scenario #2 (Mirror). This shows the virtual dentist inspecting the oral cavity by picking the dentist’s mirror from the tray and approaching towards the patient’s oral cavity.Scenario #3 (Syringe). This shows the virtual dentist performing injection by picking the syringe from the tray and approaching towards the patient’s oral cavity.Scenario #4 (Drill with no sound). This shows the virtual dentist picking the drill and approaching towards the patient’s oral cavity with no sound of the drill.Scenario #5 (Drill with sound). This shows the virtual dentist picking the drill. The drill makes the characteristic dental drill sound when approaching towards the patient’s oral cavity.

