Participants will be exposed to the virtual dental scenarios in a gradual manner. To give the participants a gradual and optimal VRET, participants will be encouraged to rate their anxiety every 35 seconds following immersion with each VR scenario exposure by means of SUDS [39]. The general rule applied during exposure therapy is that the exposure is continued until the subjective score of the patient is reduced to less than 50 % [44].The VRET which we are planning to use in the current experiment has only a limited set of stimuli. Accordingly, we have decided to have a safe cut off of ≤2 SUDS scores before moving to the next VR scenario. This criterion was earlier applied in a similar study [17]. The exposures with scenario 1, 2, 3, 4 and 5 are repeated p,q,r,s and t times respectively until SUDS score of ≤2 is achieved. For instance, when participant reaches ≤2 SUDS with VR scenario of sitting idle on the dental chair then the next VR scenario of inspecting the oral cavity with a dental mirror is introduced. In subsequent sessions, the intensity of VR experiences will be progressively increased from a less threatening scenario to a more threatening scenario to make the simulation more realistic while focusing on areas of particular stress. For example, if a dental phobic participant report a fear of drills, the exposure is progressively increased from Scenario-1 (less fear evoking –‘Sitting in the dental chair’) to Scenario-5 (more fear evoking –‘Drill with sound’). To this end, situational cues that are simulated with VR scenarios are presented by the therapist in a well-controlled manner. During the simulated dental procedure participants will be asked to keep their mouth open similar to real dental experience from Scenario #2 (Examination with mirrors) through Scenario #5 (Drill with sound) and are advised to follow the instructions of the researcher, for example ‘to open their mouth really wide’. The added stimulus such as keeping the mouth open will be standardized and applied to all the participants. Participants will receive the therapy in one long session for 150 minutes with a 10-min break/s to avoid simulator sickness. If the participant’s SUDS rating has not decreased to 2 with any of the VR scenarios within 30 minutes of exposure the researcher will continue with the next VR scenario. The session will be video recorded for future validations and analysis of the subject’s body response during the VRET exposure.

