## Data analysis

The analyses will be performed based on the Consolidated Standards of Reporting Trials (CONSORT) statement regarding e-health [47]. An independent biostatistician will carry out the statistical analysis using SPSS 20.0.The recorded data will be labelled so that the biostatistician will not be able to distinguish between the two groups. All data will be analyzed using an intention-to-treat analysis. We will also conduct a per protocol analyses. Descriptive statistics will be calculated, whereas discrete variables will be summarized by frequencies or proportions. Continuous variables will be reported as means and standard deviations or medians and range (depending on the measurement level of the variables). Data will be checked for differences at T0, T1, T2, T3 and T4 between the VRET and informational pamphlet group using independent samples t-test. Between-group changes at post treatment will be calculated by using a 2 (pre-treatment/post-treatment) × 2 (VRET/Informational pamphlet) repeated measures MANOVA. Post hoc comparisons will be applied if clarification of the main effects of the MANOVA is needed. Effect sizes between the groups will be calculated with Hedges’ g. Clinical significance change analyses as described by Jacobson and Truax [48] will be conducted to determine whether the changes from pre-test to post-test are clinically significant [48]. Missing data analysis will be performed and the reason for non-adherence will be registered.

The continuous monitoring of HR data will help us determine whether the physiological changes diminish following multiple exposures with each scenario (suggestive of habituation-Reliability of therapy).

To evaluate the correlation between subjective measures of VR experience (presence, realism, nausea) with objective measure of HR during each VR scenario, only the first exposure measures will be considered to eliminate the order effects as shown in Table 2.

Since the baseline physiology levels will vary widely between individuals, we will be determining the percentage change from baseline HR during the first exposure of each VR scenario for analyses rather than considering the absolute values. The percentage change of heart rate (%HR) will be calculated as follows:$$ \%\mathrm{H}\mathrm{R} = \left(\mathrm{MeanVR} - \mathrm{MeanBaseline}\right)/\mathrm{MeanBaseline}, \times 100 $$where,

MeanVR: Mean of HR during the VRET of 1^st^ exposure of each VR scenario, and

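### SUDS ≤2 is the rule that ends each scenario, so neither reaching it nor a heart-rate fall measured up to that exposure shows habituation by itself

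*Protocol article*

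**What the plan says.** All places are in the protocol article.

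- **Secondary outcome measures**, on the SUD scale: "each VR exposure is repeated, until there is habituation demonstrated by a relatively low SUD score (≤2), and the next scenario is introduced". Ratings run from 0 to 10. The count of exposures is also recorded: "The total number of VR exposures with each VR scenario that was required to achieve SUDS score of ≤2 will be summed up".
- **Experimental phase**: "The duration of each exposure will be 35 seconds", with one rating per exposure. There is a cap: if the "SUDS rating has not decreased to 2 with any of the VR scenarios within 30 minutes of exposure the researcher will continue" with the next scenario. The section also calls the threshold a safe cut-off for moving on.
- **Data analysis**: continuous HR monitoring is to help "determine whether the physiological changes diminish following multiple exposures with each scenario (suggestive of habituation-Reliability of therapy"). No test or model is named for this trend. The %HR formula and the planned correlations use the first exposure of each scenario only.
- **Table 1**: HR and SUDS are collected in the VRET arm only.

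**The concern.** Two statements in the article combine badly. One rating of 2 or less, with no requirement that it be sustained, is called demonstrated habituation. That same rating fixes where the series ends, and HR over that series is then read as a second sign of habituation.

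When the length of a series depends on the outcome, its last point is selected. SUDS at that point is low whether or not distress was trending down. If HR varies with SUDS within a person, HR at that point is selected to be low as well. The article expects such a link: it plans to correlate SUDS with %HR to establish the validity of HR. With no HR series in the pamphlet arm, no comparison would reveal the artefact.

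At stake is a secondary conclusion, that repeated exposure produces habituation and that this supports the reliability of the therapy. The course of HR during therapy is a stated secondary objective.

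**Working it through.** The article gives no operating figure for the rule, so there is none to reproduce.

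**Inputs from the article.** Exposure 35 s; cap 30 min; stop at SUDS ≤2 on a 0–10 scale; 15 VRET participants; 5 scenarios.

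**Inputs assumed (not in the article).** Mean SUDS, within-person SD, lag-1 autocorrelation of ratings, within-person SUDS-HR correlation and within-person HR SD, all constant over exposures, so that there is no habituation.

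**Step 1: chances to stop.** 30 × 60 / 35 = 51.4, so at most 51 ratings per scenario. This is an upper bound, because giving ratings and taking breaks use time.

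**Step 2: chance of stopping without habituation.** With independent ratings and probability p of a rating ≤2 each time, P(stop) = 1 − (1 − p)^51. This is 5.0% at p = 0.001, 40.1% at 0.01, 64.3% at 0.02 and 92.7% at 0.05. With normal fluctuation and rounding, p = Φ((2.5 − mean)/SD):

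| Mean SUDS | SD | p | P(stop within 51) |
|---|---|---|---|
| 4 | 1 | 0.0668 | 97% |
| 5 | 1.5 | 0.0478 | 92% |
| 6 | 1 | 0.00023 | 1% |
| 7 | 1.5 | 0.00135 | 7% |

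The answer runs from almost never to almost always, depending on values the article does not supply.

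**Step 3: size of the HR artefact, by hand.** Take mean 5, SD 1.5, independent ratings, correlation 0.3 and HR SD 3 bpm. A stopping rating has a standardised value below (2.5 − 5)/1.5 = −1.667, with expectation −0.0995/0.0478 = −2.08. A first rating that did not stop has expectation 0.0995/0.9522 = +0.10. The expected HR change is 0.3 × 3 × (−2.08 − 0.10) = −2.0 bpm in scenarios that stop by rating, with no habituation present.

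**Step 4: simulated trials without habituation.** Settings: 15 participants, 5 scenarios, 51 exposures, person means centred on 4 or 5 with SD 1, within-person SD 1.5, autocorrelation 0 or 0.5, HR SD 3 bpm. Counted: significant falls in a two-sided 5% test (nominal 2.5%).

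- Rule met in 70–93% of scenarios that needed more than one exposure (48–81% with 20 exposures).
- First-to-last HR: false falls in about 60–76% of trials at correlation 0.3 and 95–99% at 0.5; mean spurious fall 1.3–2.6 bpm; 2–3% of trials at correlation 0.
- Plain within-person slope over all exposures: about 14–31%. Runs by mean, correlation and fit spread from 5% to 38%.
- Higher distress, correlation 0.3, first-to-last: 32–38% at mean 6, about 3–12% at mean 7 and about 4% at mean 8. At mean 6 with SD 1 it is 5.5%.

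A second set used one scenario, person means spread evenly over 4–8, SD 1–2, autocorrelation 0 or 0.8 and HR SD 4 bpm. First-to-last false falls were 2.1–2.8% at correlation 0, 4.2–20.4% at 0.3 and 5.5–61.1% at 0.6.

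**Step 5: analyses that behave differently.** Mean HR by exposure number, among those still in the scenario, does not fall. It is flat with independent ratings and rises by up to 1.1 bpm at exposure 5 with strong autocorrelation. In the second set, leaving out the stopping exposure brought the first-to-last contrast back to 2.2–2.9% with independent ratings, but only down to at most 12.9% with autocorrelation 0.8.

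**Step 6: when habituation is real.** Let SUDS fall by 0.1 to 0.4 per exposure from mean 6, with HR following it at correlation 0.5. The plain slope detects the fall in 100% of trials, the slope without the stopping exposure in over 99%, and a slope adjusted for same-exposure SUDS in only about 3–7%.

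**The case against.** The strongest reply is that the article never commits to a first-to-last HR comparison. It names no trend test, and a condensed article may leave that choice to the full protocol or analysis plan. The contrast with the largest error rate is thus not the authors' stated analysis, and a plain slope is far less affected. This stands, and it is why the point cannot be put as an error rate of the trial.

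It is also fair that participants must score MDAS ≥15 and answer yes to all four phobia items. If their distress sits at 7 or 8 with little fluctuation, the rule seldom fires by chance. The Experimental phase section already uses ≤2 for progression, under a cap.

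A reader might infer more: that the rule fires from chance alone, that it makes HR appear to fall, or that the efficacy result is compromised. The documents support none of these. They give no SUDS mean, variability or SUDS-HR correlation; at zero correlation there is no HR artefact. MDAS, DFS, VAS-A and the behavioural test are compared between arms and do not depend on where a scenario stopped. The correlations use first exposures. The hypothesis on HR following therapy can draw on a separate 10-minute recording phase.

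What the reply leaves standing is the wording: a stopping criterion is called a demonstration, and HR up to that stop is read as support for it.

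**Conclusion.** The point holds in a limited form. The last SUDS of a completed scenario is ≤2 by construction and cannot demonstrate habituation; this needs no assumption. An HR trend that includes the stopping exposure can be biased toward a fall, provided HR and SUDS are positively related within a person.

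The size of that bias is conditional. It is large for a first-to-last contrast and moderate for a plain slope at mean SUDS 4–5 with SD 1.5. It is small at stable distress of 7 or more, or at mean 6 with SD 1. Low variability alone is not protective: at mean 4 with SD 1 the rule still fires in 75–97% of scenarios. The consequence is confined to the secondary habituation claim. It is worth correcting because the change is cheap and alters what may be concluded. Nothing here bears on whether the cut-off is clinically suitable.

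**What to change.** Leave the session procedure and the cut-off as they are, and change the description and analysis:

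1. Describe SUDS ≤2 as the progression criterion only.
2. Do not report reaching it, the final SUDS, or a first-to-last HR difference as evidence of habituation.
3. Estimate the HR trend as a within-person, within-scenario slope on exposure number, leaving out the exposure that triggered the stop. Give the slope over all exposures as a sensitivity analysis.
4. Do not adjust for same-exposure SUDS in the main estimate, since that removes the shared fall in distress and arousal that habituation would produce.
5. Report the result as descriptive, and state that stopping depended on SUDS.

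**Cost.** A few sentences and one model on data already recorded. Scenarios with one or two exposures contribute nothing to the slope. Some bias remains if ratings are strongly autocorrelated (up to about 16% false falls in the settings tried). Power depends on how slopes are combined: an unweighted average of participants' slopes is less sensitive than a slope pooled in a mixed model.

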### Procedure

After arrival at the dental office, participants will receive a detailed explanation about the study from the researcher. All participants will be asked for a written informed consent to participate in the study. The participants will be interviewed to screen for dental phobia using the “Phobia checklist” by the researcher. The interview will take 0.5 to 1.5 hours. The participants will undergo the baseline assessments (T0) which will include use of questionnaires to record the participants’ characteristics such as demographic information, self-reported oral health, self-reported dental attendance and history of a bad experience with a previous dentist [42]. Completing the questionnaires will take 10-15 minutes. The interview and questionnaire are completed on the same day. Informed consent and pre-operative data will be collected in the waiting area. The participants undergo VRET at their own pace free of cost. The assessment of state and trait dental anxiety will be done utilizing the VAS-A [32], MDAS [34] and DFS [36]. After T0, the participants will be block randomized as mentioned in Fig. 1 into VRET intervention and informational pamphlet control groups.

### VRET group

#### Description of the VRET system used

The VRET software has been developed for this study by Virtual Simulations Inc in collaboration with KR and [name]. The hardware comprises of two networked computers of which the VR-simulator PC (Personal Computer) renders the virtual environment and the other User interface-PC (UI-PC) allows the therapist to control and individualize stimuli presented. The VR-simulator software will generate the VR dental environment using a Dell XPS-8700 desktop with 4th Generation Intel Core i7-4790 processor (8 M Cache, up to 4.0 GHz) and ASUS NVIDIA GEFORCE GTX 750 TI OC 2GB GDDR5 graphic card. The system will generate the display at a rate of 60 frames per second. To immerse the participants in the VR dental environment we will use an Oculus development kit 2 HMD (Head Mounted Display) with a resolution of 960X1080 per eye and with a 100 degree field of view (nominal).

#### Treatment room configuration

The waiting and VR treatment area will be shaped, using cues usually present in these areas. For VRET, a simulated dental environment will be created, with a dental chair, overhead light, dental instruments and to enhance immersion characteristic dental clinic-related smell (drops of oil of cloves on cotton wool) will be introduced. The room temperature will be maintained at 21 °C.

The treatment room where the study will be conducted will be equipped with:Two networked computers and a HMD as described above.Oculus positional tracking camera mounted on a tri-pod: To track the head movements in real-time.Logitech C-920C webcam mounted on a tri-pod: To record the video for future validations and evaluate the participant’s body response during VRET.YOGA Mini Tie Clip Condenser Microphone: To record the voice of the participants during VRET, It is synchronized with the webcam.MIO LINK HR wrist band: To record the real-time HR of the participants during therapy.SUUNTO movestick mini: For wireless transfer of HR data from the wrist band to the simulator PC.PHILIPS wireless portable speaker BT100B/37: To produce characteristic dental drill sound.

#### The simulated dental experience

The VRET system will be operated by the author of this study. Training will be provided by a clinical psychologist and Virtual Simulations Inc. When participants assigned for VRET visit the dental office the researcher records the unique reference number and initiates the VRET session. The Simulator PC, UI PC and video camera are turned on. Participants will be seated in a supine position comfortably in the dental chair and will be assisted in wearing the HMD (in OFF mode) and HR bracelet (left hand) by the researcher. Also, a hand held computer mouse will be given to the participants which acts as a panic button. The participants will hold the computer mouse with their right hand and will be instructed how to activate the panic button by clicking the mouse (under their control) when the presented scenario feels unbearable to them during the VRET session. The simulator PC is connected with the UI PC. On the UI window the researcher enters the patient/subject name, connects the UI with VR simulator by entering VR Internet Protocol address and presses the start button of the log record for real time HR recording continuously during the session.

#### Phases of VRET session: The phases are depicted in Table 2

##### Baseline phase

During this phase, the participants will see no display (Black screen) through the HMD (In OFF mode) for 10 minutes. Concurrently, the VR simulator software will record the HR. The purpose will be to record the resting HR as per HR wrist band manufacturer’s instructions.

##### Training phase

The HMD is turned ON once during the entire VRET session at this phase. In general, participants may show a higher physiological response when exposed to see something novel, this is referred to as orientation effects [43]. To overcome this, the participants in this phase will first view a surrounding 3D (3 Dimensional) stereoscopic scene of simulated dental environment through the HMD and only take a passive role by watching the interactive scene for 2 minutes. The participants are encouraged to turn his head and look around the virtual dentist’s office by way of the built-in motion tracking present in the HMD. Thus, the test subject will be lying on a real dentist chair while he will see its virtual counterpart inside the HMD as he looks around, turning his head. To allow the test subject to feel immersed in the virtual environment, we will include a generic 3D model of a person lying on the dentist chair such that when looking down, the subject will see what feels like his own body. The virtual environment seen by the patient will be displayed to the researcher on the computer screen and the HR will also be recorded.

##### Experimental phase

In this phase, participants are exposed to five different VR scenarios (Idle, Mirror, Syringe, Drill with no sound, Drill with sound). The duration of each exposure will be 35 seconds. The interactive part of the simulated dental environment will be controlled by the researcher using the tool selection option on the UI window of the computer. The researcher will be able to control the playback of the VR scenarios.

VRET is conducted using a pre-determined hierarchy as follows:Scenario #1 (Idle). This shows a dental operatory with various instruments surrounding the patient’s chair and a virtual dentist sitting next to the patient’s right hand inside the 3D scene.Scenario #2 (Mirror). This shows the virtual dentist inspecting the oral cavity by picking the dentist’s mirror from the tray and approaching towards the patient’s oral cavity.Scenario #3 (Syringe). This shows the virtual dentist performing injection by picking the syringe from the tray and approaching towards the patient’s oral cavity.Scenario #4 (Drill with no sound). This shows the virtual dentist picking the drill and approaching towards the patient’s oral cavity with no sound of the drill.Scenario #5 (Drill with sound). This shows the virtual dentist picking the drill. The drill makes the characteristic dental drill sound when approaching towards the patient’s oral cavity.

Participants will be exposed to the virtual dental scenarios in a gradual manner. To give the participants a gradual and optimal VRET, participants will be encouraged to rate their anxiety every 35 seconds following immersion with each VR scenario exposure by means of SUDS [39]. The general rule applied during exposure therapy is that the exposure is continued until the subjective score of the patient is reduced to less than 50 % [44].The VRET which we are planning to use in the current experiment has only a limited set of stimuli. Accordingly, we have decided to have a safe cut off of ≤2 SUDS scores before moving to the next VR scenario. This criterion was earlier applied in a similar study [17]. The exposures with scenario 1, 2, 3, 4 and 5 are repeated p,q,r,s and t times respectively until SUDS score of ≤2 is achieved. For instance, when participant reaches ≤2 SUDS with VR scenario of sitting idle on the dental chair then the next VR scenario of inspecting the oral cavity with a dental mirror is introduced. In subsequent sessions, the intensity of VR experiences will be progressively increased from a less threatening scenario to a more threatening scenario to make the simulation more realistic while focusing on areas of particular stress. For example, if a dental phobic participant report a fear of drills, the exposure is progressively increased from Scenario-1 (less fear evoking –‘Sitting in the dental chair’) to Scenario-5 (more fear evoking –‘Drill with sound’). To this end, situational cues that are simulated with VR scenarios are presented by the therapist in a well-controlled manner. During the simulated dental procedure participants will be asked to keep their mouth open similar to real dental experience from Scenario #2 (Examination with mirrors) through Scenario #5 (Drill with sound) and are advised to follow the instructions of the researcher, for example ‘to open their mouth really wide’. The added stimulus such as keeping the mouth open will be standardized and applied to all the participants. Participants will receive the therapy in one long session for 150 minutes with a 10-min break/s to avoid simulator sickness. If the participant’s SUDS rating has not decreased to 2 with any of the VR scenarios within 30 minutes of exposure the researcher will continue with the next VR scenario. The session will be video recorded for future validations and analysis of the subject’s body response during the VRET exposure.

Only verbal guidance and exposure techniques will be used on the participants during VRET. There will be no relaxation or other CBT-based interventions during therapy. Participants will be instructed to become as involved as possible and focus on their most frightening stimuli of the particular part of the virtual environment (describing the situation, any strange sensations and their feelings). This will be done to avoid dissociation from the VR experience. During the simulated treatment, real-time recording of the psychophysiological parameters (HR) will be determined to obtain more ‘objective’ measures of the physiological state of the participants during therapy. The HR responses obtained with different cues (Idle, Mirror, Syringe, Drill with no sound and Drill with sound) in this phase will be compared with the baseline phase (No display) to study the HR variations. The subjective measures of presence, realism and nausea (cybersickness) are recorded following the 1^st^ exposure of each VR scenario as shown in Table 2.

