A recent meta-analysis suggests VRET to be slightly, but significantly, more effective than IVET (in vivo exposure therapy) [27]. Although, VRET provides a powerful means of modifying affect, because of its immersive nature, it has not been tested yet as a therapy for dentally related anxiety or dental phobia. In an effort to answer this question, we will use VRET simulation software for the treatment of dental phobia and test its efficacy in the present study. The primary objective of the present study is to determine the efficacy of VRET versus an informational pamphlet control group in terms of dental trait and state anxiety reductions at 1 week, 3 months and 6 months follow-up among a sample of patients suffering from dental phobia. The secondary objectives are to determine (a) the real-time effect of VRET on the course of participant’s physiological response (HR) on exposure with a series of dentally related cues during therapy and (b) the relation between subjective (i.e., presence) and more objective (i.e., HR) measures during VRET. It is hypothesized that: (a) VRET would result in a significantly reduced level of dental trait anxiety [measured by MDAS (Modified Dental Anxiety Scale) and Dental Fear Survey (DFS)] and state anxiety [indexed by VAS-A (Visual Analogue Scale-Anxiety)] at 1 week, 3 months and 6 months follow-up compared to the informational pamphlet control group, (b) VRET would result in significantly higher reduced physiological arousal (i.e., HR) to dental anxious stimuli/cues relative to the baseline HR values following therapy, (c) VRET will demonstrate a positive correlation between subjective and objective measures of ‘presence’.

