Mean Baseline: Mean of HR during baseline phase of VRET session.

This will help us to compare and correlate between:Self-reported subjective scores (SUDS) and Objective scores (%HR during first VR exposure of each scenario) of anxiety. Determines the validity of HR (how well do self-report scores correlate with physiological measure of HR).Subjective measures of presence and the objective scores (%HR).Subjective measures of presence and realism.Objective scores (%HR) and subjective realism measures.Objective scores (%HR) and subjective cybersickness (nausea) measures.

The association between measures will be determined using the Pearson correlation coefficient.

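### The only stated reference for heart rate under each dental scenario is a black screen, so the contrast mixes response to the scenario with response to active VR; the in-VR training-phase recording goes unused

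*Protocol article*

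**What the plan says.** The first secondary objective (Background) is the real-time effect of VRET on the course of the participant's "physiological response (HR) on exposure with a series of dentally related cues during therapy".

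The reference for that response is fixed in two places:

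- Experimental phase: heart rate under each of the five scenarios "in this phase will be compared with the baseline phase (No display) to study the HR variations".
- Data analysis: "we will be determining the percentage change from baseline HR during the first exposure of each VR scenario for analyses", with the denominator given as "Mean Baseline: Mean of HR during baseline phase of VRET session".

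The Baseline phase section defines this reference: "the participants will see no display (Black screen) through the HMD (In OFF mode) for 10 minutes".

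A training phase of 2 minutes lies between baseline and the first scenario. Its stated reason is that "participants may show a higher physiological response when exposed to see something novel, this is referred to as orientation effects", and it is meant to overcome this. Participants "will first view a surrounding 3D (3 Dimensional) stereoscopic scene of simulated dental environment through the HMD" and are encouraged to turn the head and look around. The virtual scene is "displayed to the researcher on the computer screen and the HR will also be recorded"; Table 2 also marks heart rate in this phase. Neither the Experimental phase section nor Data analysis uses this recording.

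**The concern.** A scenario and its reference differ in at least two respects: the headset display is on, and a dental scenario is shown. A difference between them is the sum of both effects. If being in active VR raises heart rate, all five scenarios will appear arousing whether or not their content contributes anything.

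This bears on what the trial can report. The Background calls the effect of VRET on heart rate inconclusive for want of well-designed studies, and finds no published work on VRET-induced arousal in anxious dental patients. A report of arousal to dental cues that rests on the black-screen contrast alone would not fill that gap. A reference closer to the scenarios is already being recorded.

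**Working it through.** **Figures in the plan.** The article gives no heart-rate mean, SD, power or test, so there is no figure of its own to reproduce. Everything numerical below is an illustration under stated assumptions.

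**1. What the stated measure contains.** The Data analysis formula is %HR = (MeanVR − MeanBaseline) / MeanBaseline × 100. Write MeanVR = B + v + c, where B is black-screen heart rate, v the effect of active VR and c the effect of the scenario. Then %HR = 100 × (v + c) / B, so v enters every scenario in full.

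With an assumed B = 75 bpm and c = 0:

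| v (bpm) | %HR by the plan's formula |
|---|---|
| 0 | 0.0 |
| 2 | 2/75 = 2.7 |
| 5 | 5/75 = 6.7 |
| 10 | 10/75 = 13.3 |

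**2. How small an offset would matter.** Assume all 15 VRET participants contribute and each scenario is tested against baseline with a paired t-test (df 14, two-sided 5%). The protocol does not name this test. The mean shift that just reaches significance is 2.145 × SD/√15:

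| Assumed SD of %HR | Shift | At 75 bpm |
|---|---|---|
| 4% | 2.2% | 1.7 bpm |
| 6% | 3.3% | 2.5 bpm |
| 8% | 4.4% | 3.3 bpm |

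At SD 6% and no scenario effect, a VR-only rise of 3% (noncentrality 3/(6/√15) = 1.94) would be significant 44% of the time. A rise of 5% (noncentrality 3.23) would be significant 85% of the time.

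**3. What the training-phase reference does and does not repair.** Take B = 75, v = 5 and a dental effect c = 5 for Idle, so heart rate in Idle is 85.

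- Against the black screen: 10/75 = 13.3%.
- Against a VR reference free of dental content (not available in this trial): 5/80 = 6.25%.
- Against the training phase, if the virtual surgery already evokes none, half or all of the dental effect: 5/80 = 6.25%, 2.5/82.5 = 3.0%, or 0/85 = 0%.

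The training reference removes v, but also whatever dental response the virtual room itself evokes. The loss should be largest for Idle, which shows a dental operatory with instruments and a seated dentist and so is close to the training view. Mirror, Syringe and the two Drill scenarios add an instrument approaching the mouth, which the described training view does not contain.

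**4. Which planned analyses a uniform offset touches.**

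- Scenario against baseline, and the level of %HR: affected in full.
- Pearson correlations of %HR with SUDS, presence, realism and nausea: adding one constant to every %HR value leaves the coefficient unchanged.
- Decline over repeated exposures of a scenario: a constant offset cancels.
- Primary comparison of VRET with pamphlet on anxiety: heart rate is a secondary measure in the VRET arm only (Table 1), so it is not involved.

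**The case against.** Five points can be made for the plan.

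- **The novelty effect is already handled.** The training phase exists to absorb the orientation response before the scenarios begin. This stands in part: the novelty component of v should be smaller by Scenario 1. It does not show that the rest of the response to active VR has gone, and the black-screen contrast cannot show it.
- **The training phase is not a clean control.** A reader might infer that heart rate there is recorded before any dental cue. The text does not support that: the scene is a virtual dentist's office with a body on the dental chair, which is a dental stimulus for a phobic participant. It precedes only the five scenario cues. Heart rate there may also be raised by the orientation response and by the head turning that participants are encouraged to do. Resting every statement about a cue on this one contrast could hide real arousal.
- **A resting baseline suits some of the stated aims.** The hypothesis of reduced arousal after therapy is worded relative to baseline heart rate, and the objective speaks of the effect of VRET. This stands, and it is why the black-screen contrast should be kept. It does not support attributing the difference to the individual scenario.
- **Other differences remain.** The mouth is kept open in Scenarios 2 to 5, and participants describe their feelings during exposure. A training-phase reference removes neither. These add to the confounding of the black-screen contrast and do not justify it.
- **Further contrasts may sit in an analysis plan that is not shown.** That is possible. The point here is narrower: the article names a comparator and builds it into the formula, and that comparator cannot isolate a scenario.

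**Conclusion.** The point holds as a limit on interpretation. As written, the contrast of each scenario with a black screen measures the response to VRET as a whole. It cannot by itself support a claim of response to a particular dental cue, while an in-VR recording that would help is used in no stated analysis.

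The size is unknown. The 2.7 to 13.3% apparent response rests on an assumed 75 bpm and assumed VR effects. The 44% and 85% rates rest in addition on an assumed SD, 15 evaluable participants, no scenario effect and a test the protocol does not specify. A reader might take these as the trial's false-positive rates; the documents support no such reading.

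Nor does the point undermine the heart-rate programme as a whole. The correlations and the habituation analysis survive a uniform offset, and the randomised comparison is unaffected. The change is worth making because it is nearly free, but the trial does not depend on it.

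**What to change.** In the Experimental phase and Data analysis sections:

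1. Keep the black-screen contrast and %HR as defined, and describe them as the response to VRET as a whole.
2. Add two sets of within-participant contrasts: the first exposure of each scenario against the later part of the training phase, and the first exposures of Scenarios 2 to 5 against that of Idle. Fix the training window before the data are examined; the article offers no basis for a particular length.
3. Claim a scenario-specific response only where these within-VR contrasts support it.
4. State the limits. The training view is a dental room and may carry residual orientation response and head movement, so the contrast is conservative, most of all for Idle. The open mouth in Scenarios 2 to 5 stays confounded in both sets of contrasts. The trial has no dental-free VR reference.

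The cost is a few further paired contrasts on heart rate already recorded, and some wording. No new measurement or change of procedure is needed. The downside is that a conservative reference may miss a real response, which is why both references should be reported side by side.
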